### Statistical analysis

In model 1 we test whether treatment outcomes improve during the active treatment phase across (i.e. pooled for) all three groups to test for the overall efficacy of the GSH program. This model thus contains one within-subjects factor (pre-post). In model 2 we test whether the temporal course of GSH program’s outcomes during active treatment and during follow-up varied among the three groups (TG, CG1, and CG2). We will apply a two-way mixed analysis of variance with group (three levels) as between-subjects and time (pre-post or post-follow-up) as within-subjects factors, whereby we are interested in the interaction between group and time.

Power analyses: based on prior research data (e.g. [25]), we expect an 18% dropout rate for our power estimations. The correlation (rho) of the number of weekly binges between the two time points is estimated to be around 0.6 (using data published in [14]). Here we assume a slightly more conservative value of rho = 0.5. Based on alpha = 0.05 (two-sided), beta = 0.2, a medium effect size (Cohen’s f = 0.25), and a dropout rate of 18%, the estimated sample size is 34 based on model 1 and 42 (14 per group) based on model 2. Taking the larger of these two values (42) this value was subsequently increased to 60 (20 per group) to be on the safe side with respect to the required sample size.

Analyses based on the secondary goal will include moderators and mediator models.

Analyses for the third (compare the present Internet-based treatment with available data from a face-to-face therapy and conventional GSH program with a book) and fourth goal (explore usability) are of exploratory nature and will thus use descriptive statistics such as means, standard deviations, and percentages.

Multilevel models will be used to analyze the data of the first and second goals [50], including multilevel structural equation models (for mediator models in second goal [51]).

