Disorder specific psychotherapy (cognitive behavioral therapy [CBT] and interpersonal psychotherapy [IPT]) have proven to be successful in reducing binge-eating symptomatology in the short and long term (e.g. [11–15]). Several studies have shown that among different BED treatment approaches (e.g. CBT and IPT) and settings (group or individual), up to 79% of the patients benefit from the therapy and show abstinence from binge-eating at the end of the active treatment [11, 16]. Maintenance of the therapy success in follow-up periods from 12 months up to five years has been proven in different studies from our group [13, 15]. The most thoroughly validated moderator for treatment success in BED is the reduction of binge-eating episodes by 65–70% within the first four treatment sessions (“rapid response”) (e.g. [13, 16]). A negative predictor of treatment success is over-evaluation of shape and weight. Also, the initial level of psychopathology seems to negatively influence treatment effects and it has been shown that therapeutic interventions are generally less successful with increasing duration of the ED [11, 16, 17]. The combination of pharmacotherapy and psychotherapy is not superior to psychotherapy alone and psychopharmacological medication in BED is still at an off-label-use level. Consequently, the spread and improvement of psychological treatments for BED is necessary [1] and Internet-based guided self-help (GSH) treatments are valuable treatment alternatives in BED therapy [1, 11, 18, 19].

The recently published NICE guidelines for the recognition and treatment of EDs strongly recommend GSH as the initial treatment provided in a stepped care approach [1]. CBT-based GSH treatments – in comparison to other BED related GSH – show the most pronounced positive outcomes [11, 18]. CBT GSH has been showed to be more effective compared to a waitlist control group, an unspecific therapy, and a weight-loss program. Abstinence rates of binge-eating in disorder-specific GSH were up to 64% with a significant reduction of psychopathology after treatment and at 12-month follow-up [20].

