### Material and measures

The content of the eight sessions and three follow-up sessions is all derived from established and evaluated treatment material [12–15, 39, 48, 49].

In Table 1, an overview of the main contents of each session is given.

**Table 1 Tab1:** Main content of therapy sessions

Session	Content
0	Introduction to the program
1	Individual etiological model of BED
	Self-observation of eating behavior
2	Motivation
	Goal attainment scale
3	Regular eating
	Analyzing binge-eating episodes with the ABC-model
4	Developing strategies to overcome binge-eating (trigger and reaction control)
5	Positive/enjoyable activities
	Working with emergency cards
6	Expanding strategies
	Dysfunctional thoughts
7	Dysfunctional thoughts and body image
	Reduction of overweight
8	Setting longer-term goals
	Coping with future difficulties
	Relapse prevention
Follow-up sessions 1–3	Further goals
	Coping with current difficulties
	Relapse prevention

Table 2 gives an overview of all instruments that will be applied during the study. Primary outcome variables are number of binge-eating episodes and ED pathology. Secondary outcome variables are reduction of depressive symptoms and increase of the level of functioning. Moreover, all exercises that the patients edited during the sessions as well as all communication between the therapist and the patients will be stored and evaluated (e.g. regarding treatment integrity).

**Table 2 Tab2:** Instruments

Instrument	Description/Construct	Time point
Interviews		
Diagnostic interview for psychiatric disorders, short version (Mini-DIPS; [53])	Structured interview to assess psychiatric disorders according DSM-5. Duration: approx. 45 min.	t_1_, t_2_
Eating Disorder Examination (EDE; German version [54])	Structured interview to assess eating disorder pathology Duration: approx. 45 min.	t_1_
Therapists ratings		
Clinical global impression scale [55]	Measure of symptom severity, treatment response and the efficacy of treatments in patients with mental disorders. 7 items rated by the clinician.	t_1_, t_2_
Self-report questionnaires		
Sociodemographic questions (own items)	Sociodemographic questions (gender, age, nationality, sick leave days, prior treatments etc.). 35 items.	t_1_
Patient’s expectancies regarding the therapy (own items)	Questions to assess attitude and expectations of the patients towards the internet-based treatment. 5 items.	t_1_

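### Model 2's group-by-time test on two time points compares raw change scores; adjusting for the t1 value would cut the error variance by 25% at the plan's own correlation

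*Protocol article*

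**What the plan says.** The Statistical analysis section defines model 2 as a two-way mixed ANOVA with three groups and "time (pre-post or post-follow-up) as within-subjects factors, whereby we are interested in the interaction between group and time". It covers the active treatment phase and the follow-up phase. No baseline covariate is named.

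The trial is sized on this test. On the correlation the section says "The correlation (rho) of the number of weekly binges between the two time points is estimated to be around 0.6", then "Here we assume a slightly more conservative value of rho = 0.5". The other inputs are "Based on alpha = 0.05 (two-sided), beta = 0.2, a medium effect size (Cohen’s f = 0.25), and a dropout rate of 18" per cent. The result is that "the estimated sample size is 34 based on model 1 and 42 (14 per group) based on model 2", and "this value was subsequently increased to 60 (20 per group) to be on the safe side".

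On outcomes, Material and measures states: "Primary outcome variables are number of binge-eating episodes and ED pathology". The section on aims expects the treatment group to improve more over the first four weeks than the two control groups combined, and expects similar courses in all three groups afterwards. The Statistical analysis section closes by naming multilevel models for the first and second goals, without saying how baseline enters.

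**The concern.** A change score subtracts the whole baseline value whatever its correlation with the later value. When that correlation is below 1, this subtracts too much and leaves avoidable noise. Regressing on baseline subtracts only the predictable part. With 20 patients per group, the difference affects the width of every group comparison. It also matters where the groups are expected to be alike, because a claim of similar courses is only as good as its confidence interval.

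**Working it through.** **Inputs (Statistical analysis section).** Three groups, two time points, alpha 0.05 two-sided, power 0.80, f = 0.25, rho = 0.5 (estimate 0.6), dropout 18%, N = 60 as 20 per group.

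**1. The plan's own figures.** The repeated-measures non-centrality is lambda = f² × N × 2/(1−rho).
- Model 1, N = 34: lambda = 0.0625 × 34 × 2/0.5 = 8.5 on 1 and 33 df, power 80.8%.
- Model 2, N = 42: lambda = 0.0625 × 42 × 2/0.5 = 10.5 on 2 and 39 df, power 80.3%. With N = 39, power is 76.9%.

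Both stated sizes reproduce, but as numbers before dropout: 42/0.82 gives 52 to randomise. The final 60 covers this, since 60 × 0.82 = 49.2 completers.

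**2. The interaction is a change-score test.** On a generated data set with three groups of 16, the group-by-time F of the mixed ANOVA and the one-way F on post-minus-pre differences were both 0.198470.

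**3. Variances, with equal SD sigma at both times.**
- Change score: 2(1−rho) sigma².
- Baseline-adjusted: (1−rho²) sigma².
- Ratio: (1−rho²)/[2(1−rho)] = (1+rho)/2.

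The ratio is 0.75 at rho = 0.5 and 0.80 at rho = 0.6. Confidence intervals shrink to √0.75 = 0.866 and √0.80 = 0.894 of their width.

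**4. Effect on model 2, pre to post.** Randomised groups share the same expected t1 mean, so the expected group difference is the same either way. Lambda is multiplied by 2/(1+rho), and one error df is lost.

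| rho | Power, change score, 49 completers | Power, adjusted | N for 80%, change score | N for 80%, adjusted |
|---|---|---|---|---|
| 0.5 | 86.8% | 94.8% | 42 | 33 |
| 0.6 | 93.4% | 97.4% | 36 | 30 |

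At rho = 0.5, lambda goes from 0.0625 × 49 × 4 = 12.25 to 12.25/0.75 = 16.33.

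**5. Four-week contrast, treatment group against both control groups.** Analysable: 20 × 0.82 ≈ 16 and 40 × 0.82 ≈ 33. The standard error is sqrt[v(1/16 + 1/33)] with v in units of sigma². At rho = 0.5, v = 1.00 for the change score and 0.75 adjusted. From the non-central t, the difference detectable with 80% power falls from 0.871 to 0.755 SD, and power at 0.8 SD rises from 0.730 to 0.843. The article assigns no specific test to this contrast, so this shows what a change-score test would cost if carried over.

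**The case against.** **The power is already there.** At f = 0.25 and N = 60, model 2 has about 87% power after dropout, and no difference is expected. This stands: there is no shortfall at the planned effect. But under the plan's convention, one group differing equally from the other two has f² = d²/18, so f = 0.25 means d = 0.25 × √18 = 1.06 SD. Smaller differences have less room, and a claim of similar courses gains from narrower intervals.

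**Model 2 is not the four-week test.** Correct. A reader might infer that the plan throws away a quarter of the information in its main randomised contrast. The article does not support that, because neither model 1 nor model 2 is assigned to that contrast.

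**Baseline is not clean in model 2.** This also stands. In the post-to-follow-up form, the earlier value is post-treatment. In the pre-post form, the control groups start the programme after four weeks of waiting, and the article does not say whether their pre value is taken before or after it. This limits which value may be the covariate; it does not remove the case for the t1 value.

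**Multilevel models are named.** They do not settle the matter. A group-by-time multilevel model with a freely estimated baseline in each group keeps the same contrast.

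**Binges are counts, so a log link is needed.** A reader might infer this from the many zeros to be expected after treatment; the Background says "Abstinence rates of binge-eating in disorder-specific GSH were up to 64" per cent. But that is an upper figure from other programmes, and the article gives no mean, dispersion or rate ratio. In simulations on assumed inputs (16 per group, baseline mean 4 binges a week, realised rho 0.34 to 0.50, rate ratio 0.5 to 0.6), power was 8 to 23% for the change score, 22 to 48% for linear adjustment and 35 to 54% for a log-link model. The ranking is plausible, but the sizes are products of the assumptions. In a separate set of 800 runs per cell, the log-link test's type I error reached 0.075 in one cell. A count model also cannot serve ED pathology.

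**Conclusion.** The point holds for linear baseline adjustment. Model 2 as stated is a raw change-score test, and adjusting for t1 lowers the error variance by 25% at the plan's rho (20% at 0.6). At the planned effect, power goes from about 87% to 95%. This is an avoidable loss of precision. It neither invalidates the test nor leaves the trial underpowered for it.

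The figures assume equal SDs at both times, the stated rho between t1 and post, and 49 completers. They apply where the change score runs from t1 to post. If the controls' pre value is taken after waiting, or for post to follow-up, the relevant correlations are not given and no gain is claimed. There, adjusting for t1 also changes the question, to a comparison of levels at the later time. The figures for 16 against 33 are illustrative, and any further gain from a log link cannot be computed from the document.

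**What to change.** - For group comparisons, model the post and follow-up outcomes with the t1 pre-randomisation value as covariate, or fit a multilevel model with a t1 mean common to all groups. Do this for binge episodes and for EDE-Q, and keep the change-score result as a sensitivity analysis.
- Do not use a post-waiting or post-treatment value as the covariate. State which assessment is the pre value in the control groups.
- Reconcile the ANOVA and multilevel statements, so that one model and one handling of baseline is named.
- Apply the same adjustment to the four-week comparison on the weekly binge counts. Table 2 does not list the WBQ at t1, so name the EDE or EDE-Q at t1 as the source of baseline binge frequency.
- Optionally, analyse binge counts with an overdispersed log-link model. The price is a rate ratio in place of a mean difference.

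The cost is analysis-plan wording, since EDE and EDE-Q are already taken at t1. A week-4 EDE-Q analysis is different: Table 2 lists that instrument at t1, t2 and t3 and shows no week-4 assessment, so it applies only if one is actually collected.

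### The sample sizes of 34 and 42 are said to allow for 18% dropout, but at the stated inputs they are the numbers needed with no dropout at all

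*Protocol article*

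**What the plan says.** All of this is in the power paragraph of the protocol article, Methods, Statistical analysis.

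- Dropout is announced as part of the calculation: "we expect an 18% dropout rate for our power estimations".
- The correlation between the two time points is put at about 0.6 from earlier data, and then lowered: "Here we assume a slightly more conservative value of rho = 0.5".
- The other inputs are given as "Based on alpha = 0.05 (two-sided), beta = 0.2, a medium effect size (Cohen’s f = 0.25").
- Dropout then appears last in the list of inputs, directly before the results: "and a dropout rate of 18%, the estimated sample size is 34 based on model 1 and 42 (14 per group").
- The larger figure, 42, is raised in a separate step: "this value was subsequently increased to 60 (20 per group) to be on the safe side".

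Model 1 is the pooled pre-post comparison ("This model thus contains one within-subjects factor (pre-post")). Model 2 is the interaction of group (three levels) with time (two levels).

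**The concern.** On the plain wording, 34 and 42 are recruitment numbers that already cover an 18% loss, and the move from 42 to 60 is extra safety on top. If dropout was not in fact included, the stated requirement does not deliver the stated power. Most of what looks like reserve is then needed just to reach the target.

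This matters if recruitment falls short. A reader who trusts the paragraph would conclude that stopping somewhat above 42 still leaves 80% power after dropout.

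**Working it through.** **Inputs** (all from the power paragraph): two-sided alpha 0.05; power 0.80; f = 0.25; rho = 0.5; dropout 18%; m = 2 time points; one pooled group for model 1 and three groups for model 2.

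**Formula.** Power comes from the noncentral F distribution for repeated-measures ANOVA, with noncentrality λ = f² × N × m / (1 − rho). Here λ = 0.0625 × N × 2 / 0.5 = 0.25 N. Degrees of freedom are (1, N − 1) for model 1 and (2, N − 3) for the model 2 interaction.

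**Step 1: reproduce the printed figures, with no dropout.**

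| Model | N | λ | Power |
|---|---|---|---|
| 1 | 33 | 8.25 | 0.795 |
| 1 | 34 | 8.50 | 0.808 |
| 2 | 39 (13 per group) | 9.75 | 0.769 |
| 2 | 42 (14 per group) | 10.50 | 0.803 |

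The smallest N reaching 0.80 is 34 for model 1. For model 2 in equal groups it is 42. Both printed figures are matched to the patient with zero loss. The other convention for f (λ = f² × N) would need 128 and 159, so it is not the one behind the printed figures.

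**Step 2: apply the 18% loss.**

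- Model 1: 34 / 0.82 = 41.5, so 42.
- Model 2: 42 / 0.82 = 51.2, so 52. Per group, 14 / 0.82 = 17.1, so 18, which is 54 in total.
- The cruder inflation N × 1.18 gives 41 and 50 (17 per group, 51).
- Inflating the unrounded requirements (33.37 and 41.69) gives 40.7 and 50.8, so 41 and 51.

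No version returns 34 and 42.

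**Step 3: what the printed figures would deliver after 18% loss.**

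- Model 1: 34 × 0.82 = 27.9, about 28 patients, power 0.72.
- Model 2: 42 × 0.82 = 34.4, about 34 patients, power 0.70.

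**Step 4: what the planned 60 delivers.**

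- 60 × 0.82 = 49.2, about 49 patients. Model 2 power is 0.87 and model 1 power is 0.93.
- Reserve as the text implies it: 60 − 42 = 18.
- Reserve over the dropout-adjusted requirement: 60 − 54 = 6, or 60 − 52 = 8.
- At 30% loss, 60 × 0.70 = 42, where model 2 power is 0.803. The target is just met and nothing is left over.

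**The case against.** **Another route leads to the same figures.** The paragraph names two correlations. At rho = 0.6 the unrounded requirements are 27.10 for model 1 and 34.01 for model 2. Divided by 0.82 they become 33.05 and 41.48, which round up to 34 and 42. So dropout may have been applied, with 0.6 used instead of 0.5. The article does not show the power output, so it cannot settle which slip occurred.

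That much stands, but it does not rescue the text. This route contradicts the explicit statement that 0.5 is assumed. It also works only if inflation comes before rounding: whole-patient requirements at rho = 0.6 are 28 and 35 (36 in equal groups), and dividing those by 0.82 gives 35 and 43 (44). Either way the printed figures do not follow from the printed inputs, and the correct figures at those inputs are the same.

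**The consequence is small.** Nobody plans to recruit 34 or 42. The planned 60 exceeds 54 and keeps power above 80% at the assumed loss. This stands, and it limits the weight of the point.

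**The 30% scenario is one choice among several.** The article's Discussion ties 30% to the group's longer face-to-face treatment. It gives 13% for their eight-week treatment, and 9% and 19.1% for Internet programmes. The 18% assumption is within that range. The 30% case shows only where the reserve ends; it is not a forecast.

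**The text never states a reserve of 18.** True; that figure is the difference between 60 and 42. But because dropout is listed among the inputs of 42, reading the later increase as the dropout allowance is strained.

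**Conclusion.** The point holds. For the inputs the article prints, 34 and 42 are analysable numbers with no loss. The requirement with 18% dropout is 42 for model 1 and 52 for model 2 (54 in equal groups). The stated model 2 requirement is therefore short by 10 to 12 patients, and the reserve at 60 is 6 to 8 rather than 18.

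The trial as planned still meets its power target on its own assumptions, with model 2 power of about 0.87 at 18% loss. The error is in the justification, not in the enrolment figure. It should be corrected because it would mislead any decision to accept fewer than 60.

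The conclusion rests on the F-test formula above, which reproduces both printed figures exactly, and on taking models 1 and 2, f = 0.25 and rho = 0.5 as given.

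**What to change.** Rewrite the sample size sentence to say the following: at the stated inputs, 34 (model 1) and 42 (model 2, 14 per group) analysable patients are needed; allowing for 18% dropout, 42 and 54 (18 per group) must be randomised; 60 (20 per group) will be randomised, which leaves about 49 analysable patients and about 87% power for model 2 at f = 0.25.

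Before publishing the correction, the authors should check their power output to see whether dropout was left out or rho = 0.6 was used. The restated figures are right for rho = 0.5 in either case.

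The cost is one corrected sentence. Enrolment, allocation and analysis do not change.

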### Ethical considerations

Ethics approval was given by the Ethics Committee of the canton Bern (Switzerland). Project-ID: 2017–00102. All participants will be informed in accordance with the study protocol approved by the Ethics Committee (clinical study protocol version 4, 06.07.2017).

## Discussion

The present RCT evaluates a newly developed CBT-based GSH program delivered via the Internet. Next to accessibility and independence of time and location, another benefit of such a manualized program is the clear focus on the disorder-specific factors in treatment. The results of the present study will allow recommendations regarding suitabilty and efficacy of low-threshold interventions for patients suffering from BED [17].

We postulate several advantages for this clinical trial. First, the treatment duration of approximately 11 weeks (including diagnostics) is shorter than in the studies by Carrard et al. [25] (6 months) and de Zwaan et al. [27] (4 months). In our face-to-face treatment studies, a longer treatment period has been associated with a higher dropout rate of 30% [14] compared to 13% dropouts in a shorter, eight-week treatment [12]. Carrard et al. [26] reported dropout rates of 9% (2/22 participants in the Internet-based treatment group) and de Zwaan et al. [28] of 19.1% (17/89 participants in the GSH intervention). Second, we will apply an Internet-based version of our original BED treatment program [39], which has been systematically evaluated in RCTs in face-to-face group settings. This will enable us to indirectly compare the efficacy of the Internet-based BED treatment with data from previous studies [12–15]. Third, and for the first time in BED research, the present study investigates the role of interventions to increase positive expectations (placebo) regarding the upcoming treatment.

The efficacy, usability, and adoption of the developed program will be evaluated through interviews, questionnaires, and analysis of interaction logs. In respect of psychotherapy research, the present study provides the possibility of examining the efficacy of a standardized disorder-specific treatment programm in comparison to a pure waiting period and a placebo-inspired intervention. Even if we make the rather conservative assumption that the specific intervention during active treatment is the “verum” that results in positive outcome and the “placebo” is not effective, we could nevertheless assume that the placebo-inspired CG shows advantages in terms of a faster positive development during treatment due to higher positive expectations and a more established therapeutic relationship already at the beginning of the active treatment. Such a result would refer to an “add-on effect” of a placebo-inspired waiting period or in other words of a preparation phase before a disorder-specific treatment, which would be relevant for clinical practice. The comparison of the present GSH program with established face-to-face therapy and a book-based GSH program, as well as the investigation of moderating and mediation variables, will improve the understanding of differential indications in BED treatment.

This research will also help to understand the specific interaction traits of users following an Internet-based treatment and to gather requirements for user interfaces that support their needs and reduce the risk of therapy drop-out. Another expected contribution of this research in the field of human–computer interaction is the exploration of mechanisms to adapt automatically the content or alerts of the therapy according to the patient specificities, towards user-induced adaptation [52] and personalized therapy.

To sum up, the development of an Internet-based BED treatment increases the feasibility to recruit larger patient groups with less subject burden in terms of time and loss of anonymity for patients. Better knowledge about the effect and the determinants of the effect of Internet-based treatments might potentially lead to more cost-effective approaches to intervention. From a scientific point of view, larger samples from the general population suffering from BED will allow more fine-grained research on moderators and mediators of change in the future. This information will enrich etiological models and might stimulate the development of additional treatment modules, which are easily implemented in the Internet-based treatment (e.g. training of emotion regulation, emotion regulation in interpersonal relationships, etc.).

The Internet-based GSH program could be adapted for other EDs such as AN and BN or individuals suffering from EDs not further specified. It could also prove useful for groups of patients with specific profiles such as non-responders, adolescents, and older patients, or as a support during transfer from inpatient to outpatient treatment (especially when the patient has to wait for a specialized BED outpatient treatment). The question of the intensity and quality of the psychotherapeutic support/guidance (e.g. via email contact) will also be addressed and whether guidance could also be provided by non-specialists (i.e. a person without a psychotherapeutic background). After investigating efficacy under controlled research conditions, the GSH program will be implemented into daily clinical practice and its effectiveness evaluated.

